# RadBone: bone toxicity following pelvic radiotherapy – a prospective randomised controlled feasibility study evaluating a musculoskeletal health package in women with gynaecological cancers undergoing pelvic radiotherapy

**DOI:** 10.1136/bmjopen-2021-056600

**Published:** 2022-06-14

**Keywords:** radiotherapy, musculoskeletal disorders, gynaecological oncology, clinical trials

## Abstract

**Introduction:**

Patients receiving radiotherapy are at risk of developing radiotherapy-related insufficiency fractures, which are associated with increased morbidity and pose a significant burden to patients’ quality of life and to the health system. Therefore, effective preventive techniques are urgently required. The RadBone randomised controlled trial (RCT) aims to determine the feasibility and acceptability of a musculoskeletal health package (MHP) intervention in women undergoing pelvic radiotherapy for gynaecological malignancies and to preliminary explore clinical effectiveness of the intervention.

**Methods and analysis:**

The RadBone RCT will evaluate the addition to standard care of an MHP consisting of a physical assessment of the musculoskeletal health, a 3-month prehabilitation personalised exercise package, as well as an evaluation of the fracture risk and if required the prescription of appropriate bone treatment including calcium, vitamin D and—for high-risk individuals—bisphosphonates. Forty participants will be randomised in each group (MHP or observation) and will be followed for 18 months. The primary outcome of this RCT will be feasibility, including the eligibility, screening and recruitment rate, intervention fidelity and attrition rates; acceptability and health economics. Clinical effectiveness and bone turnover markers will be evaluated as secondary outcomes.

**Ethics and dissemination:**

This study has been approved by the Greater Manchester East Research Ethics Committee (Reference: 20/NW/0410, November 2020). The results will be published in peer-reviewed journals, will be presented in national and international conferences and will be communicated to relevant stakeholders. Moreover, a plain English report will be shared with the study participants, patients’ organisations and media.

**Trial registration number:**

NCT04555317.

Strengths and limitations of this studyThe RadBone is the first randomised controlled trial to assess a musculoskeletal health package aimed to prevent radiotherapy-related insufficiency fractures.A feasibility economic evaluation will allow future assessment of this complex intervention’s cost-effectiveness.Planned longitudinal proteomic analyses may reveal mechanistic insights and promising treatment targets.A prospectively published detailed protocol increases the transparency and allows for peer review of the methodology used.This study is not blinded and lacks an active comparator, hence, it is susceptible to performance and detection bias.

## Introduction

In 2015, there were 2.5 million people in the UK with a diagnosis of cancer and this number is expected to rise to 4 million by 2030.^1^ As a result of the continuing improvement in early detection of disease and improved treatment efficacy, a significant proportion are living long beyond their cancer diagnosis. However, estimates suggest that currently over 500 000 people living with and beyond cancer have one or more physical or psychosocial consequences of their cancer or its treatment that affect their lives on a long-term basis. These consequences also have a substantial implication in terms of National Health Service (NHS) resources.

Patients receiving radiotherapy are at risk of developing radiotherapy-related bone toxicity, in particular radiotherapy-related insufficiency fractures (RRIFs). Incidence of RRIFs following pelvic radiotherapy has been reported between 1.7% and 89% and occurring between 3 and 20 months post-radiotherapy. The wide variation in reported incidence depends on imaging modality and radiological reporting standards, symptomatic versus asymptomatic fractures, radiotherapy dose and underlying tumour type.^2^ A recent meta-analysis of over 400 patients with RRIFs following pelvic radiotherapy for gynaecological cancers suggested an overall incidence of 14%.^3^ Over 30 studies have been published since the 1990s describing >1000 patients with pelvic RRIFs. This literature is notable for being almost exclusively retrospective in nature, a sparsity of baseline assessment of bone density and fracture risk, the absence of patient-reported outcome measures (PROMs) used to assess quality of life (QOL) and no primary preventative or secondary management intervention studies.^4 5^

The devastating effects of osteoporotic fragility fractures on morbidity and mortality and the economic cost are well described.^6^ Pelvic insufficiency fractures may also increase mortality^7^ but these data reflect an elderly population with multiple comorbidities and the applicability to the pelvic radiotherapy population is not well defined. In addition, there are no pelvic RRIF studies reporting QOL as an outcome measure. However, the anxiety, pain, reduced mobility and increased morbidity associated with these have been described, with a number of patients requiring hospital admission for assessment and pain control.^8^ Therefore, formal studies of QOL and PROMs are much needed, considering the wide range of pelvic radiotherapy toxicities.^9^

While a small number of studies, confirmed in a recent meta-analysis,^3^ suggest osteoporosis as a risk factor in pelvic RRIFs, unlike the strong evidence base for bisphosphonate use in primary and secondary prevention of fragility fractures, there is no such evidence for RRIFs.^5^ A small non-controlled study demonstrated intravenous zolendronic acid administration prior to spinal radiotherapy led to a lower prevalence of radiotherapy bone toxicity than expected^10^ and a single randomised prospective study in patients undergoing spinal radiotherapy for metastatic disease demonstrated that intravenous zolendronic acid reduced urinary markers of collagen cross-linking.^11^

Contradictory data from animal studies around the protective effects of bisphosphonates on RRIFs limit our understanding of the pathophysiology and therapeutics of RRIFs. Animal studies using whole mouse radiation have demonstrated an early activation of bone resorption in the 5 days following low dose (2 Gy) of radiotherapy which was reduced by subcutaneous administration of risedronate immediately following irradiation.^12^ In contrast, a focal radiation technique in mice (using a small animal radiation research platform), arguably a more physiological representative method of irradiation, demonstrated that alendronic acid did not prevent the radiation-induced trabecular bone loss but that this was prevented by blocking osteoblast apoptosis with PTH 1–34.^13^

The RadBone is the first open-label prospective randomised controlled trial (RCT) to determine the feasibility and acceptability of a musculoskeletal health package (MHP) intervention in women undergoing pelvic radiotherapy for gynaecological malignancies and inform power calculations for a definitive RCT. Moreover, this feasibility trial will also explore potential implications on the incidence of RRIFs, QOL and other clinical effectiveness and safety outcomes, as well as providing indicative estimates of the intervention’s cost-effectiveness.

## Methods and analysis

### Study design

See figure 1.

**Figure 1 F1:**
[figure not shown]
Recruitment, randomisation process and description of the stratified interventions (#: fracture). BP, blood pressure; DXA, dual-energy X-ray absorptiometry; FRAX, fracture risk assessment.

### Study setting

The planned study is a prospective randomised controlled feasibility trial of 80 patients with gynaecological malignancy (cervical and endometrial) undergoing pelvic radiotherapy at the Christie Hospital NHS Foundation Trust in Manchester, UK (a tertiary referral oncology centre). The study opened for recruitment in May 2021, and the estimated primary completion date is in November 2022 and study completion date in June 2023.

### Eligibility criteria

Individuals aged over 18 years, with a histologically confirmed endometrial or cervical cancer undergoing potentially curative or adjuvant radiotherapy will be eligible, provided they are able and willing to provide an informed consent to participate.

The exclusion criteria are: (i) age <18 years or >85 years; (ii) pre-existing bone conditions such as osteoporosis treated with bisphosphonates in the previous 5 years, fibrous dysplasia, osteogenesis imperfecta or other metabolic bone conditions; (iii) home address outside Greater Manchester; (iv) contraindication or intolerance of magnetic resonance scanning.

### Interventions

Women undergoing radiotherapy for a gynaecological malignancy will be randomised to an observation group and will receive standard assessment and care, following the current local clinical pathway, or an intervention group that will receive an MHP, in addition to standard assessment and care and will be followed for 18 months.

Patients randomised to the MHP arm will receive (i) a physical assessment of musculoskeletal health and a 3-month prehabilitation personalised exercise package as part of the Greater Manchester Prehab4Cancer programme,^14^ (ii) a fracture risk assessment (FRAX) based on baseline dual-energy X-ray absorptiometry (DXA) bone mineral density (BMD) and (iii) treatment for bone health according to national UK recommendations, that is, standard of care for prevention of fragility fractures, by being subdivided into three groups (low risk, medium risk and high risk).

Patients with a normal BMD and a FRAX score below the National Osteoporosis Guideline Group (NOGG) recommended treatment line will be considered low risk. Medium risk is defined as osteopenia on the DXA, with FRAX score below the NOGG treatment line. Finally, those with osteopenia and a previous vertebral or hip fracture, or a FRAX score above the NOGG recommended treatment line will be considered high risk.

Low-risk patients will be provided with a copy of the Royal Osteoporosis Society ‘healthy living for strong bones’ leaflet. In addition to the leaflet, medium-risk patients will receive calcium (1000 mg once daily) and vitamin D (800 IU/day) supplementation. The same interventions will be offered to high-risk patients, who will also undergo secondary osteoporosis screening (blood tests) and will receive oral alendronate 70 mg once weekly, in the absence of contraindications. Annual intravenous zolendronic acid infusion will be considered as an alternative where appropriate.

Those randomised to the observation arm will remain blinded to the results of the evaluations until the end of the study unless a fragility fracture or RRIF develops during the study.

#### Prehabilitation exercise programme (Prehab4Cancer)

All patients randomised to the MHP arm of the study will be offered a bespoke prehabilitation exercise programme via the Prehab4Cancer programme in Greater Manchester. The MHP arm patients will be referred to the Prehab4Cancer team via electronic referral immediately following randomisation. Allocated patients will be individually assessed by the Prehab4Cancer team according to their usual protocols and assigned an appropriate prehabilitation programme. Duration of the programme is 12 weeks from the first assessment and participation will be encouraged, as tolerated. The Prehab4Cancer and recovery programme is community-based, which incorporates exercise (cardiovascular and muscle strengthening/resistance training), nutritional screening and advice and well-being support. Further details of programmes’ assessment tools and the stratification of interventions are described by Moore *et al*^14^ and can be found in www.prehab4cancer.co.uk. The current scope of this protocol is to evaluate feasibility of participants’ engagement in this face-to-face and remote prehabilitation service both pretreatment and during treatment.

### Baseline and follow-up evaluation

As described in figure 2, baseline evaluations will include a bone health assessment with DXA BMD measurement and completion of a bone health questionnaire. PROMs will also be captured. Finally, fasting serum and plasma blood samples will also be collected.

**Figure 2 F2:**
[figure not shown]
Study flow chart; assessments and outcome time-points. C+R, consent and randomisation; CV, clinic visit; DXA, dual energy X-ray absorptiometry; EBRT, external beam radiotherapy; eGFR, estimated glomerular filtration rate; HR, high risk; MHP, musculoskeletal health package arm; NHS, National Health System; Ob, observational arm.

At 6, 12 and 18 months postradiotherapy, all patients will undergo a pelvic MRI assessment for RRIFs, PROMs assessment and fasting blood sampling. During the final visit, at 18 months, all patients will have a DXA BMD scan and physical assessment of their musculoskeletal health. If signs or symptoms compatible with an RRIF are described outside the study visits study participants will be assessed and managed following the current clinical pathways.

#### Imaging studies

DXA scans of the total hip, femoral neck, L1–L4 spine and Trabecular Bone Score (TBS) assessments will be performed on a single DXA scanner (Hologic Horizon A SN 300792M V.5.6.07 with TBS V.3.0.2 calibrated to the above scanner) at the Christie NHS Foundation Trust as per local protocol. These will be undertaken by two technicians trained in conducting DXA. Images will be reviewed, validated and interpreted by the lead investigator ([name]). The femoral neck BMD (g/cm^2^) will be used in conjunction with a standardised DXA questionnaire to complete FRAX calculation.

Pelvic MRI scans will be performed at 6, 12 and 18 months on a 1.5 T MRI scanner at the Christie Hospital by trained radiographers in accordance with the study imaging protocol. Four pelvic sequences will be performed per patient (5 mm slice thickness, field of view 400 mm; coronal T1, coronal Short Tau Inversion Recovery (STIR) (inversion time 150 ms), axial T1 and axial STIR (inversion time 165 ms). These will correspond to routine follow-up scans where possible. All bone sequence scans will be dual reported by two consultant radiologists who will document the presence of fracture and their confidence in its presence, fracture location, fracture line, bone marrow oedema and other abnormalities.

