### Outcomes

The primary outcomes for this feasibility study will inform the design and power calculations for a definitive UK multicentre RCT. These are:

Eligibility and screening rate: proportion of patients eligible for the study from patient population (assessed at baseline).Recruitment and study group allocation rate: number and proportion of eligible patients recruited, randomised and allocated to appropriate study populations (assessed 2 weeks postconsent).Intervention fidelity rate: number and proportion of patients completing the elements of the study (assessment visits, prehab exercise programme, prescribed medications, QOL questionnaire) (assessed at the end of study, at 18 months).Attrition rate: number of patients lost to follow-up (assessed at the end of study, at 18 months).Patient and physician acceptability assessed with electronic questionnaires (change from baseline assessed at 6, 12 and 18 months).Health economic analysis: within-trial cost-effectiveness analysis to demonstrate feasibility of health economic data collection and analysis in a multicentre RCT (change from baseline assessed at 6, 12 and 18 months).

The secondary outcomes are:

Incidence of pelvic RRIF (assessed at 6, 12 and 18 months postradiotherapy).Longitudinal change in BMD and fracture risk using FRAX (assessed at baseline and 18 months).Longitudinal change in biochemical markers of bone turnover (change from baseline assessed at 2, 3, 4, 5, 6, 7, 8 and 9 weeks and at 6, 12 and 18 months).QOL assessment: adapted CTCAE pelvic questionnaire and SMFA adapted to lower limbs (change from baseline assessed at 6, 12 and 18 months).

Exploratory end points include identification of predictive markers of RRIFs (radiomic, proteomic, BMD) and exploratory measurement of proteomic biomarkers of bone turnover during pelvic radiotherapy.

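### MRI readers are not stated to be masked and no pre-radiotherapy reference read is listed, so RRIF percentages are open to avoidable detection bias and may include earlier fractures

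*Protocol article*

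**What the plan says.** All references are to the protocol article.

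- **Readers (Imaging studies).** "All bone sequence scans will be dual reported by two consultant radiologists who will document the presence of fracture". They also record their confidence, the location, any fracture line and marrow oedema. The section does not say what the readers know about allocation or treatment, or how a disagreement is settled. The scans coincide with routine follow-up imaging where possible.
- **Blinding (strengths and limitations list).** "This study is not blinded and lacks an active comparator, hence, it is susceptible to performance and detection bias". The Introduction calls the trial open-label. The only masking described is under Interventions, where women in the observation arm are kept unaware of their own results.
- **Timing of MRI (Imaging studies).** "Pelvic MRI scans will be performed at 6, 12 and 18 months on a 1.5 T MRI scanner".
- **Baseline (Baseline and follow-up evaluation).** "baseline evaluations will include a bone health assessment with DXA BMD measurement and completion of a bone health questionnaire", together with patient-reported outcomes and blood samples. No MRI is named.
- **Outcome (Outcomes, secondary).** "Incidence of pelvic RRIF (assessed at 6, 12 and 18 months postradiotherapy".
- **Earlier fracture.** The eligibility criteria do not exclude it as such, and under Interventions "those with osteopenia and a previous vertebral or hip fracture, or a FRAX score above the NOGG recommended treatment line will be considered high risk".
- **Use of the result (Statistical and health economic analysis).** No hypothesis about effect is tested. The descriptive analysis centres on the RRIF percentage in each arm and on risk factors for RRIF, and it informs the power calculation of the definitive trial.

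**The concern.** Whether an MRI shows an insufficiency fracture is partly a matter of judgement, as the recording of reader confidence shows. The Introduction says of published rates: "The wide variation in reported incidence depends on imaging modality and radiological reporting standards", before naming further causes. In an unblinded trial, a reader who knows the arm may call doubtful oedema differently in the two groups. Patients and treating staff cannot be masked to exercise or tablets, but image readers can be.

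The second issue is separate. An incidence needs a starting point free of the event, or at least a known one. With the first listed MRI 6 months after radiotherapy, nothing in the article shows how a fracture already present before treatment would be told apart from a new one.

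The two mechanisms act on different quantities. Reading influenced by knowledge of the arm can distort the contrast between arms. Earlier fractures are balanced by randomisation in expectation, so they mainly raise the level in both arms. They can also distort the risk-factor and predictive-marker analyses: an old fragility fracture plausibly goes with low bone mineral density, so low density could appear to predict RRIF for reasons unrelated to radiotherapy. At stake are the planning figures for the next trial, not an efficacy conclusion from this one.

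**Working it through.** **1. The plan's own figure.** Sample size section: 40 per arm and 15% attrition. 40 × (1 − 0.15) = 34, which agrees with the stated minimum of 30. There is no power calculation to reproduce.

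**2. Inputs.** From the Introduction: an overall RRIF incidence of 14%. Assumed, because the documents give no values: the reading error rates, the share *p0* of women with an earlier fracture, and a halving of incidence as the effect of interest.

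**3. Reading that differs by arm.** Observed proportion = p × Se + (1 − p) × (1 − Sp), with true p = 0.14 in both arms.

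| Se/Sp, observation | Se/Sp, MHP | Observed, observation | Observed, MHP | Spurious difference |
|---|---|---|---|---|
| 0.95/0.95 | 0.95/0.95 | 17.6% | 17.6% | 0 |
| 0.95/0.95 | 0.85/0.98 | 17.6% | 13.6% | 4.0 points |
| 0.95/0.90 | 0.85/0.98 | 21.9% | 13.6% | 8.3 points |

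Example, row 2: 0.14 × 0.95 + 0.86 × 0.05 = 0.176, and 0.14 × 0.85 + 0.86 × 0.02 = 0.136. More simply, if only the false-positive rate differs, by 2, 5 or 10 points, the spurious difference is 0.86 × 0.02, 0.05 or 0.10 = 1.7, 4.3 or 8.6 points. A true halving of 14% is 7 points. Equal error in both arms creates no difference where there is none.

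**4. Earlier fractures counted as events.** Apparent incidence = p0 + (1 − p0) × 0.14, assuming that the earlier fracture is still visible and is called.

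| p0 | Apparent incidence | Extra events per 34 women |
|---|---|---|
| 1% | 14.9% | 0.3 |
| 2% | 15.7% | 0.6 |
| 5% | 18.3% | 1.5 |
| 10% | 22.6% | 2.9 |

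True events expected: 34 × 0.14 = 4.8. With the same p0 in both arms, a true difference of 7 points shrinks to (1 − p0) × 7, for example 0.95 × 7 = 6.65 points. The level moves and the contrast hardly does.

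**5. Sampling error.** The nearest whole count to 4.8 is 5. For 5/34 = 14.7%, the exact (Clopper-Pearson) 95% interval is 5.0% to 31.1%. For the difference between two arms of 34 at 14%, the standard error is √(2 × 0.14 × 0.86 / 34) = 0.084, so the 95% half-width is about 1.96 × 0.084 = 16.5 points. Both exceed the shifts in steps 3 and 4.

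**6. Effect on planning (illustration).** Two proportions, 80% power, two-sided 5%, variance pooled under the null:

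- 14% v 7%: 300 per arm.
- Planning on half of an apparent 18.3% (18.3% v 9.15%): 221 per arm.
- If earlier fractures at 5% are also counted in the definitive trial (18.3% v 11.65%): 451 per arm needed.

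Under these assumptions, an inflated level makes the definitive trial too small.

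**The case against.** The strongest reply is that the article is silent on these points rather than wrong. The Imaging studies section says nothing about what the readers know, and it refers to a study imaging protocol that is not shown and may require masked reading. Not blinded and open-label describe the trial, not the radiologists. A reader might infer that the radiologists are unmasked, or that they see notes revealing prehabilitation or bone drugs. Neither is stated. The shared use of routine scans makes the second possible and no more.

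A reader might also infer that pre-existing fractures are counted as incident. No counting rule is given. The outcome is by name radiotherapy-related, nothing forbids comparison with older images, and the study flow chart (figure 2) is not shown.

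The published range of 1.7% to 89% cannot be put down to reading alone: the Introduction also names imaging modality, symptomatic status, dose and tumour type. A fixed MRI protocol, scheduled scans for everyone and dual reporting already limit several of these sources.

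Finally, RRIF is secondary, detection bias is disclosed, no effect is tested, the illustrative inputs are assumed, and sampling error is larger than the shifts.

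All of that limits the point, but it does not remove it. Detection bias arises in outcome assessment, and the article accepts it without saying that the one step that can readily be masked is masked. Disclosure does not reduce a bias. A confidence interval displays imprecision but not bias, and a larger trial shrinks only the former.

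**Conclusion.** The point holds as a cheap and worthwhile improvement. As written, the article leaves the RRIF contrast between arms open to avoidable detection bias. It also leaves open that the RRIF level and the risk-factor analyses include fractures that predate radiotherapy. It does not show that either occurs.

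The size of both effects is unknown. The figures above (spurious differences of 1.7 to 8.6 points; apparent incidence of 14.9% to 18.3% for earlier fractures in 1% to 5% of women) rest wholly on assumed error rates and prevalences. With about 34 women per arm, sampling error is larger than any of them. It would go too far to say that earlier fractures bias the comparison between arms. Randomisation balances them in expectation, although chance imbalance is possible at this size. The consequence is for the estimates carried into the definitive trial, and no conclusion about efficacy is affected.

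**What to change.** 1. State that the same two radiologists read each study MRI independently from de-identified worklists, masked to arm and bone treatment, and that disagreements are settled by masked consensus between them. If the study imaging protocol already requires this, one sentence saying so is enough.
2. Have them also review pre-treatment pelvic imaging where it is already on file, such as a staging MRI or the radiotherapy planning scan. Its availability is an assumption. Report RRIF incidence excluding fractures visible there, with the all-fracture figure alongside.
3. Keep RRIFs found through symptoms between visits in the incidence count, flagged by source and read masked where imaging allows. Moving them out could lose true events that are no longer visible at the next scheduled scan.

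This concerns the research read and the reporting only. Sample size, visits and treatment do not change.

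**Cost:** de-identification work and up to about 80 extra reads of existing images, with no new scan and no new reader. **Downside:** where only a planning CT exists, the reference read is less sensitive, so some earlier fractures would still be missed. Reporting both figures, and the type of reference image available for each woman, makes this visible.
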